## Expectedness

Expectedness will be determined according to the Summary of Product Characteristics (SmPC) for Cardene SR.

## SUSAR Reporting

A serious adverse event (SAE) occurring to a participant should be reported to the REC that gave a favourable opinion of the study where in the opinion of the Chief Investigator the event was ‘related’ (resulted from administration of any of the research procedures) and ‘unexpected’ in relation to those procedures. Reports of related and unexpected SAEs should be submitted within 15 working days of the Chief Investigator becoming aware of the event, using the HRA [report of serious adverse event](http://www.nres.npsa.nhs.uk/docs/forms/Safety_Report_Form_(non-CTIMPs).doc) form (see HRA website).

See Appendix C for a SAE reporting flow-chart.

## Steering Committee

Although this is an experimental medicine study a Steering Committee will be convened to review the study protocol and to receive progress reports throughout the study. All SAEs will be reported to the committee chair person and SARs and SUSARS will be reported to the committee chair person immediately. The Committee will hold meetings as required (which may be by teleconference) and make recommendations to the CI and/or Sponsor.

The yellow card system will be used to notify the MHRA of any SAEs related to the study medication (<https://yellowcard.mhra.gov.uk/> ).

## Criteria for the Termination of the Study

The study is not designed to evaluate the efficacy of nicardipine on mood symptoms and therefore stopping rules based on criteria for demonstration of a robust effect or clear lack of effect are not appropriate.

## Procedure for Accounting for Missing, Unused, and Spurious Data.

The majority of the outcome measures are provided by participants via TC, PANAS, daily cognitive tests and the carrying of activity monitors and smartphones. Adherence to these rating will be reviewed regularly and any concerns about missing ratings will be addressed with the participant at the next appointment. In addition to this, where possible, participants who do not complete weekly TC ratings will be contacted and asked to complete the ratings over the phone.

## Inclusion in Analysis

The main statistical analyses will be per protocol with data for all participants being included up to the point where they stop study treatment or complete the randomised phase.

# DATA MANAGEMENT

## Source Data

Source documents are where data are first recorded, and from which participants’ Study-CRF data are obtained. These include, but are not limited to clinical and office charts, laboratory and pharmacy records, diaries, and correspondence.

Study-CRF entries will be considered source data if the Study-CRF is the site of the original recording (i.e. where there is no prior written or electronic record of data). All documents will be stored safely in confidential conditions. On all Study-CRFs except the Informed Consent Form, the participant will be referred to by non-personal identifiable information not by name.

## Access to Data

Direct access will be granted to authorised representatives from the Sponsor, Oxford University, and the regulatory authorities to permit study-related monitoring, audits and inspections.

## Data Recording and Record Keeping

All study data will be entered on to paper CRFs and/or a validated database for which Standard Operating Procedures are in place. Participants will be identified by non-personal identifiable information in any study specific database.

Data will be retained for 5 years after last visit last patient (LVLP).

# QUALITY ASSURANCE PROCEDURES

The study will be conducted in accordance with the current approved protocol, GCP, relevant regulations.

Reports of SAEs will be reviewed by the Steering Committee (See 10.7)

# SERIOUS BREACHES

In the event that a serious breach is suspected the Sponsor must be contacted within 1 working day. In collaboration with the C.I., the serious breach will be reviewed by the Sponsor and, if appropriate, the Sponsor will report it to the REC committee.

# ETHICAL AND REGULATORY CONSIDERATIONS

## Declaration of Helsinki

The CI will ensure that the study is conducted in accordance with the principles of the Declaration of Helsinki.

## Guidelines for Good Clinical Practice (GCP)

The CI will ensure that the study is conducted in full conformity with relevant regulations and with the Guidelines for Good Clinical Practice.

## Approvals

The protocol, informed consent form, participant information sheet and any proposed advertising material will be submitted to an appropriate Research Ethics Committee (REC), and HRA for written approval.

The Investigator will submit and, where necessary, obtain approval from the above parties for all substantial amendments to the original approved documents.

## Reporting

The CI shall submit once a year throughout the study, or on request, an Annual Progress report to the REC Committee, HRA, host organisation and Sponsor. In addition, an End of Study notification and final report will be submitted to the same parties.

## Participant Confidentiality

The study staff will ensure that the participants’ anonymity is maintained. The participants will be identified only by non-personal identifiable information on the Study-CRFs and any study-specific electronic database. Contact details for all participants will be stored separately from their data. This will be held in a locked cupboard at the NIHR-CRF and destroyed once they are no longer required for the follow-up call. All documents will be stored securely and only accessible by the Research Team and authorised personnel. The study will comply with the General Data Protection Regulation and Data Protection Act 2018, which requires data to be anonymised as soon as it is practical to do so.

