| **Treatment duration** | 2-week randomised phase |
| **Follow up duration** | 1 week |
| **Planned Accrual Period** | 2 years |
| **Intervention** | Nicardipine SR |
| **Formulation, Dose, Route of Administration** | Nicardipine sustained release 30mg taken twice daily.  Matched placebo. |

| **Objectives** | **Outcome Measures/Endpoints** |
| --- | --- |
| Primary objective:  To compare the effects of nicardipine and placebo on measures of cognitive instability.  . | Primary outcome measure: Cross sectional and longitudinal assessments of cognition |
| Secondary objectives  1. To compare the effects of nicardipine and placebo on variability in neural dynamics during MRI and MEG scans. This will include scans during resting state and whilst performing neuropsychological tasks.  2. To explore the effects of nicardipine on physical activity and sleep.  3. To develop a profile of calcium channel expression and calcium signalling with and without nicardipine treatment.  4.Heart rate variability  5. Mood instability | Secondary outcome measure   1. Blood oxygen level dependent signal during rest and during cognitive testing; induced and evoked field activity 2. Activity monitor measurements:   2a. Actigraphy data from a maximum of two wearable units, allowing analysis of indices of:   1. Frequency and amplitude of movements during daytime activity   ii. Categorisation of activity types.   1. Duration, timing, and quality of sleep.   2b. Sleep quality indicator questionnaire (SCI; self-report sleep measure (Espie, 2014)).  3. Measure effects of nicardipine on leucocyte calcium channel expression and calcium signalling  4. Change in R-R interval variability   1. Changes in mood instability as defined using root mean square of the successive differences (RMSSD) |

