## Post-study follow-up

Participants will be contacted following cessation of study treatment to review the status of any reported adverse events (AEs) and to check for any unreported AEs.

Please see Appendix A for a diagram of the participant pathway in the study and assessments at each visit.

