## 8.6. Post-study follow-up

Participants will be contacted within a fortnight of study completion, usually by phone, following cessation of study treatment to review the status of any reported Adverse Events and to check for any unreported AEs.

Please see Appendix B for a schedule of procedures during the study duration.

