## Discontinuation/Withdrawal of Participants from Study Medication

Each participant has the right to withdraw from the study at any time. In addition, the Researcher may discontinue a participant from the study at any time if s(he) considers it necessary for any reason including:

- Pregnancy
- Ineligibility (either arising during the study or retrospectively having been overlooked at screening)
- Significant protocol deviation
- Significant non-compliance with treatment regimen or study requirements
- An adverse event which requires discontinuation of the study medication or results in inability to continue to comply with study procedures
- Disease progression which requires discontinuation of the study medication or results in inability to continue to comply with study procedures
- Withdrawal of Consent
- Loss to follow up

When a participant stops study medication or withdraws consent, all study data collection will be stopped. Data and samples collected prior to withdrawal will be retained and the reason for withdrawal, if given, will be recorded. Where appropriate, the participant will be asked for a final set of ratings and blood samples and be advised on ongoing treatment, if relevant. If withdrawal is due to an adverse event, the researcher will arrange for follow-up visits or telephone calls until the adverse event has resolved or stabilised. Participants will be asked to return all of the devices they had been given at the beginning of the study as outlined in the devices agreement signed at the start of the study (see appendix M).

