Any pregnancy occurring during the clinical study and the outcome of the pregnancy should be recorded and followed up for congenital abnormality or birth defect, at which point it would fall within the definition of “serious”.

Causality

The relationship of each adverse event to the study medication must be determined by a medically qualified individual according to the following definitions:

*Related:* The adverse event follows a reasonable temporal sequence from study medication administration, cannot reasonably be attributed to any other cause.

*Not Related*: The adverse event is probably produced by the participant’s clinical state or by other modes of therapy administered to the participant.

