*Incidental findings:* Incidental findings. Delete current paragraph and replace with: ‘We anticipate that a subset of participants will meet criteria for an axis I/II disorder. At the discretion of the investigator, and with the permission of the participant, their GP will be informed, and the participant advised to seek advice about treatment’. Participants will also be referred to their GP for any unexpected health issues.

In the unlikely event of seeing any structural abnormalities on an MRI scan, the scan will be checked by a clinical specialist. If the specialist feels that the abnormality was medically important, they will discuss the implications with the participant and arrange for further investigations as necessary. Participants will not be informed unless the doctor considers the finding has clear implications for their current or future health. It is important to note that scans are not carried out for diagnostic purposes, and therefore the scans are not a substitute for a clinical appointment. Rather, the scans are intended for research purposes only.

*Intrusiveness of data gathering and nature of data gathered*

Participants will receive emails or text messages asking them to complete self-ratings but they will be able to choose the time of day when these prompts are sent. Participants who do not respond to an email or text message prompt will receive a single reminder the following day and may be contacted and asked to complete the ratings over the phone.

*Ability to consent:* Patients who are not able to give informed consent are not eligible for the study.

*Involvement of vulnerable participants:* The research is being conducted within the Oxford Health NHS Foundation Trust and the Department of Psychiatry at the University of Oxford and more junior researchers will be able to consult a study psychiatrist should they have any concerns about the mental state of a participant. If a participant were to become unwell during the study permission would be sought to contact their care team (GP or psychiatrist). It will be made clear to all participants that taking part in the study is in addition to routine care and that, if they feel unwell during the course of the study, they should contact their GP or care team.

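### Contact details may be destroyed, and data collection stopped, before the pregnancy and adverse-event follow-up that the protocol requires is closed

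*Protocol*

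**What the plan says.** - **Retention of contact details (Protocol 15.5, Participant Confidentiality).** They are stored apart from the study data, under lock, and "destroyed once they are no longer required for the follow-up call". No other purpose for keeping them is named.
- **The follow-up call (8.6, Post-study follow-up).** "Participants will be contacted within a fortnight of study completion", usually by phone. The synopsis gives a follow-up of one week instead. Section 6.5 states the purpose of the contact: "to review the status of any reported adverse events (AEs) and to check for any unreported AEs".
- **Pregnancy (10.1, Definitions).** For any pregnancy during the study, "the outcome of the pregnancy should be recorded and followed up for congenital abnormality or birth defect". A congenital anomaly or birth defect is on the list of serious events.
- **Adverse events (10.2).** Those that meet the recording threshold are followed until they resolve or are judged stable. No time limit is set.
- **Stopping study medication (8.11).** Pregnancy is among the reasons for which the researcher may discontinue a participant. The section then says: "When a participant stops study medication or withdraws consent, all study data collection will be stopped". The same paragraph asks, where appropriate, for final ratings and blood samples. If the withdrawal is due to an adverse event, "the researcher will arrange for follow-up visits or telephone calls until the adverse event has resolved or stabilised".

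**The concern.** Two stated rules pull against the follow-up duties. This is a conflict between rules in the protocol, not a detail that a statistical analysis plan would supply.

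First, the only reason given for holding contact details is a call early after Visit 3, but two duties can run well past that call: pregnancy outcome, and any recorded adverse event that is still open. Staff who apply 15.5 as worded, together with its sentence on anonymising data as soon as practical, could discard the means of contact while a duty is open.

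Second, 8.11 stops all data collection when medication stops and makes a follow-up exception only for adverse-event withdrawals. A participant discontinued because of pregnancy falls under the stop and outside the exception, yet 10.1 wants the outcome recorded.

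At stake is the collection of a safety outcome that the protocol itself classes as serious. Section 10.3 does not fill the gap, because its reporting period for serious events ends when study treatment has been stopped.

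**Working it through.** There is no sample-size, power or alpha figure to reproduce. The check sets the rules side by side, followed by date arithmetic and a rough count.

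**1. Rules side by side**

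| Situation | Duty | Retention under 15.5 | Data collection under 8.11 |
|---|---|---|---|
| Pregnancy found on treatment, medication stopped | Record and follow outcome (10.1) | For the call only | Stopped, no exception |
| Pregnancy found after treatment is completed | Record and follow outcome (10.1) | For the call only | Stop aimed at early discontinuation, no conflict needed |
| Withdrawal due to an adverse event | Visits or calls until resolved or stable (8.11, 10.2) | For the call only | Exception stated |
| Medication stopped for another reason, recorded event open | Follow until resolved or stable (10.2) | For the call only | Stopped, exception does not reach it |
| Treatment completed, recorded event open at the call | Follow until resolved or stable (10.2) | For the call only | Stop aimed at early discontinuation, no conflict needed |

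The retention gap runs through every row. The 8.11 conflict is sharpest for pregnancy.

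**2. Latest scheduled call**

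Appendix B puts Visit 3 at day 28 ± 2, so at day 30 at the latest. Adding the fortnight in 8.6: 30 + 14 = day 44. With the synopsis figure: 30 + 7 = day 37.

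**3. Distance to a pregnancy outcome**

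Assumption, not in the documents: conception between day 0 and day 30, birth 35 to 40 weeks (245 to 280 days) later.

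- Earliest birth: 0 + 245 = day 245. Gap from day 44: 245 − 44 = 201 days, about 29 weeks.
- Latest birth: 30 + 280 = day 310. Gap from day 44: 310 − 44 = 266 days, 38 weeks.
- With a call on day 37, the gaps are 208 and 273 days.

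The outcome therefore always falls long after the call. The gap for adverse events cannot be computed, because their follow-up has no time limit. The schedule in Appendix B lists no pregnancy test at Visit 3, so a conception during treatment might come to light only around or after the call.

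**4. How many pregnancies**

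Assumptions, not in the documents: 20 to 30 women among the 40 randomised, and a pregnancy rate of 1% to 9% per year.

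Expected number = women × annual rate × weeks / 52.

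- Over the four study weeks: 20 × 0.01 × 4/52 = 0.015, up to 30 × 0.09 × 4/52 = 0.21.
- Conceived during the two treatment weeks on nicardipine (half the women): 20 × 0.5 × 0.01 × 2/52 = 0.004, up to 30 × 0.5 × 0.09 × 2/52 = 0.05.

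The first range matches the scope of 10.1, which covers any pregnancy during the study. The second is the narrower count of pregnancies exposed to the drug. The number of adverse events open at the call cannot be estimated from the protocol.

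**The case against.** The strongest reply is that the protocol, read as a whole, is less rigid than its individual sentences.

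- **No destruction date is fixed.** Section 15.5 says only that details go when no longer needed for the call, and the call exists to review adverse events. With an event open, staff could reasonably treat the details as still needed. This stands as a possible reading, but the text does not state it, and it stretches poorly to a birth months later.
- **Section 8.11 is not absolute.** It keeps contact going after adverse-event withdrawals and asks for final assessments, and 10.2 adds an end-of-study assessment and care until stable. This stands, and it makes adverse events the secondary limb. It does not help pregnancy.
- **Other routes exist.** The GP is written to at entry, randomisation and completion, signed consent forms are kept, and participants carry a card with study-team numbers. These are partial routes. The protocol gives none of them a role in reporting a pregnancy or adverse-event outcome.
- **Cases will be rare.** Pregnancy is an exclusion, it is checked again at randomisation, and effective contraception is required. Non-serious adverse events are recorded only above a threshold. This stands, and it limits the size of the point.

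A reader might infer that safety follow-up is impossible. The open destruction date, the 8.11 exception and the partial routes do not support that. A reader might also infer that scan abnormalities must be followed to outcome. Section 15.7 asks only that, for a medically important finding, the specialist act so that "they will discuss the implications with the participant and arrange for further investigations as necessary". The scans are scheduled at Visit 2 and around Visit 3, before the call. Scans are therefore no part of this point.

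**Conclusion.** The conflict is real but narrow. The retention rule in 15.5 is not reconciled with pregnancy-outcome follow-up in 10.1 or with open-ended adverse-event follow-up in 8.11 and 10.2. The stop on data collection in 8.11 contradicts recording the outcome of a pregnancy that led to discontinuation. Followed literally, pregnancy-outcome follow-up is not secured, and follow-up of events still open at the call is secondarily exposed.

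On the assumptions shown, the outcome of an affected pregnancy falls about 29 to 38 weeks after a day-44 call, and about 0.02 to 0.2 such pregnancies are expected in the whole study. The gap rests on the assumed timing of conception and birth; the count rests on the assumed number of women and annual rate. No endpoint, analysis, power or alpha figure is affected. The point is worth correcting because the outcome concerned is one the protocol defines as serious and the correction is small.

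**What to change.** Reconcile the passages with one sentence in each of two sections.

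- **Section 15.5:** *Contact details are kept separately and securely until adverse-event and pregnancy follow-up for that participant is closed, and are then destroyed.*
- **Section 8.11:** *The stop of data collection does not apply to pregnancy-outcome and adverse-event follow-up, unless the participant refuses contact.*

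The one-week follow-up in the synopsis and the fortnight in 8.6 should be aligned at the same time, since the retention rule depends on that call.

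The cost is an amendment of two sentences with matching information-sheet wording. The downside is that contact details are held longer for the few participants with an open event or a pregnancy. For everyone else, retention is unchanged.

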## Expenses and Benefits

Participants completing the randomised phase will be given the choice of keeping the iPad or being reimbursed £50 per study visit attended. If brain scans have to be scheduled on a different day to study visits, participants will be reimbursed £25 for study visit and £25 for the brain scan visit. All participants will be able to claim reasonable travel expenses, including costs of parking for research-related visits and, for lengthy visits, will be provided with refreshments.

## Other Ethical Considerations

*Inclusion of placebo arm:* Patients with current mood instability will have a 50% chance of being allocated placebo with no active psychotropic medicine. This should not have adverse effects on patients because anyone requiring urgent treatment for mood symptoms would not eligible for the study and any participant whose mood deteriorates during the study will be encouraged to contact their GP or psychiatrist for appropriate treatment. Participants will be provided with a study treatment card which will give brief details of the study as well as contact numbers for the study team.

*Participant burden:* The study involves a number of different procedures but the time and effort required from participants to complete each of these has been kept to a minimum.

The main element of participant burden arising from the study is the time required for visits and to complete tasks.

*Visits:* The study involves a total of 3 (possibly 5) visits. The three necessary visits are for the study screening, study randomisation and the final study visit. These visits each take several hours. If MRI and MEG scans cannot be booked on the same days as these study visits, participants may have to attend a further 2 shorter visits to complete study scans. Patients will be advised of this in advance and will be provided with refreshments and breaks.

*Time:* Completion of PANAS and cognitive tasks will take about 15 minutes each day. The data collection for the continuous measures requires little input from participants apart from wearing/carrying the activity monitor and smart device neither of which should be a hindrance in any way.

Participants will also be asked to complete weekly True Colours ratings of depressive and manic symptoms.

*Genetic testing:* Participants will not be informed about the results of the genetic testing as the CACNA1C gene does not have any direct implications for health or wellbeing.

*Scans:* Completing both scans and the neuropsychological test battery will take about 5 hours. Whenever possible, participants will be able to choose whether to have the scans on the same day or on different days. Scanner operators will ensure that participants are comfortable and relaxed and will provide them with an emergency button that the participant can use at any time to indicate that they want to be released.

*Incidental findings:* Incidental findings. Delete current paragraph and replace with: ‘We anticipate that a subset of participants will meet criteria for an axis I/II disorder. At the discretion of the investigator, and with the permission of the participant, their GP will be informed, and the participant advised to seek advice about treatment’. Participants will also be referred to their GP for any unexpected health issues.

In the unlikely event of seeing any structural abnormalities on an MRI scan, the scan will be checked by a clinical specialist. If the specialist feels that the abnormality was medically important, they will discuss the implications with the participant and arrange for further investigations as necessary. Participants will not be informed unless the doctor considers the finding has clear implications for their current or future health. It is important to note that scans are not carried out for diagnostic purposes, and therefore the scans are not a substitute for a clinical appointment. Rather, the scans are intended for research purposes only.

*Intrusiveness of data gathering and nature of data gathered*

Participants will receive emails or text messages asking them to complete self-ratings but they will be able to choose the time of day when these prompts are sent. Participants who do not respond to an email or text message prompt will receive a single reminder the following day and may be contacted and asked to complete the ratings over the phone.

*Ability to consent:* Patients who are not able to give informed consent are not eligible for the study.

*Involvement of vulnerable participants:* The research is being conducted within the Oxford Health NHS Foundation Trust and the Department of Psychiatry at the University of Oxford and more junior researchers will be able to consult a study psychiatrist should they have any concerns about the mental state of a participant. If a participant were to become unwell during the study permission would be sought to contact their care team (GP or psychiatrist). It will be made clear to all participants that taking part in the study is in addition to routine care and that, if they feel unwell during the course of the study, they should contact their GP or care team.

